#### Outcomes

Primary outcomes are continuous smoking abstinence (yes or no; the percentage of participants with continuous smoking abstinence) and increased food security level (the percentage of participants with an improved food security level) 6 months after the treatment has finished. Smoking abstinence is defined as the self-reported continuous smoking cessation (≤ 5 cigarettes since the start date of their last attempt to quit) validated by the exhaled carbon monoxide test (< 10 ppm of carbon monoxide) [46]. Food insecurity is categorised into four groups: food security; mild food insecurity; moderate food insecurity; and severe food insecurity according to the Food and Agriculture Organization of the United Nations [21].

Secondary outcomes at one and 6 months post-intervention include the point prevalence of smoking abstinence, the mean number of cigarettes smoked per day, the mean number of affirmative responses on the FIES, and the health-related quality of life scores.

Time perspective will be investigated as moderator.

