### Sample size

The required sample size was calculated using the function n4prop in the package CRTSize developed for the program R (version 3.3.2) [47].

In a previous study, the smoking status of users of eight food pantries in Berlin was assessed [11]. The number of participants per food pantry in Berlin was, on average, 56 ± 12 (ranging from 36 to 73) and the number of smokers was, on average, 26 ± 8 (ranging from 19 to 41). A systematic review of recruitment strategies of smoking cessation studies revealed that studies using “active strategies” (i.e. interpersonal contact with the research team or program provider) reached from 47% up to 84% of eligible individuals, with lower participation rates among low-educated populations [48]. Therefore, a participation rate of 50% and a sample size per cluster of *n* = 13 will be assumed.

Based on the results of previous studies [49], cessation rates of 10 and 3% are assumed among participants in the intervention group and the control group, respectively.

Assuming an intra-class correlation coefficient of 0.02, a 5% significance level, and 80% power, 32 clusters are needed to detect an effect (16 in the intervention group and 16 in the control group).

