### Statistical analyses

The data will be analysed using the intention-to-treat principle, therefore including all participants irrespective of any dropouts after the baseline assessment. Missing values among the intention-to-treat population will be imputed using the baseline observation carried forward technique.

The mean, standard deviation, minimum and maximum will be given for continuous variables. Frequencies will be given for categorical variables.

To investigate differences between the intervention and the control group, independent t-tests for continuous variables and chi-square tests for categorical variables will be used. To test hypotheses 1 and 2, differences in the prolonged smoking abstinence and food insecurity improvement (the percentage of participants with an improved food security level) between the intervention and control group will be investigated using the chi-square test adjusted for intraclass correlation within clusters [50]. To account for the nesting of participants within the food pantry, mixed models with the logit link function will be used to predict cessation and food security improvement. To test hypothesis 3, a structural equation model will be used [51]. This identifies if the intervention condition predicts smoking cessation (path A), if smoking cessation predicts improvement in food security level (path B), if the intervention condition predicts the improvement in food security level (path C), and if the impact of the intervention condition on the improved food security level will be attenuated when controlling for smoking cessation.

Secondary outcomes will be analyzed accordingly.

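### The plan names only an unclustered t-test for continuous variables and does not settle whether the continuous secondary outcomes are analysed with allowance for the randomised pantries

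*Protocol article*

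**What the plan says.** All references are to the protocol article.

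- **Outcomes.** Besides the point prevalence of abstinence, the secondary outcomes are "the mean number of cigarettes smoked per day, the mean number of affirmative responses on the FIES, and the health-related quality of life scores". The section on objectives and hypotheses adds body-mass-index.
- **Statistical analyses, comparison of arms.** After the descriptive statistics, the text says that "independent t-tests for continuous variables and chi-square tests for categorical variables will be used" to investigate differences between intervention and control. It does not say whether this concerns baseline characteristics, outcomes or both.
- **Statistical analyses, clustered methods.** A chi-square test adjusted for intraclass correlation is given for hypotheses 1 and 2. Mixed models with a logit link are given for cessation and food security improvement. All of these are binary.
- **Statistical analyses, secondary outcomes.** The section closes with one sentence: "Secondary outcomes will be analyzed accordingly".
- **Sample size.** "Assuming an intra-class correlation coefficient of 0.02, a 5% significance level, and 80% power, 32 clusters are needed to detect an effect". The pantries are split equally between the arms, with 13 participants per pantry. The ICC is given for the cessation calculation, and none is given for a continuous outcome.
- **Measures.** The FIES and the SF-12 are completed at t0, as are the quantity-frequency index and the FTND.

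**The concern.** An independent t-test treats the 416 participants as 416 independent observations, although allocation was made for 32 pantries. Any similarity among users of one pantry then makes the standard error too small. The article itself gives reasons to expect some similarity: users are assigned to pantries mostly by postal code, counselling is given in groups, and the environmental measures act on the whole pantry.

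The closing sentence on secondary outcomes does not give an analyst a usable rule. There are three ways to read it:

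1. The t-test sentence covers outcomes. The named test then ignores the design.
2. The t-test sentence covers baseline only. The secondary outcomes then inherit an adjusted chi-square test and a logit model, neither of which fits a mean.
3. The closing sentence means that nesting is to be allowed for. The model for a continuous outcome is then unnamed, and a t-test without a cluster term is still the only method in the text for such a variable.

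At stake are p-values and confidence intervals for cigarettes per day, FIES responses, quality of life and body-mass-index. A second, smaller matter is precision: no method named for these outcomes uses the t0 value.

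**Working it through.** **Inputs.** Cluster size m = 13, 16 pantries per arm, ICC 0.02 and a 5% level, all from the Sample size section. Check: 32 × 13 = 416, the stated total.

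**The plan's own cluster count and the sidedness of the test.** The article does not say whether 5% is one- or two-sided. For 10% versus 3%:

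- Design effect DE = 1 + (13 − 1) × 0.02 = 1.24.
- Clusters per arm k = (critical value + power quantile)² × [0.10 × 0.90 + 0.03 × 0.97] × DE / (0.07² × 13) = (sum of quantiles)² × 2.318.
- Two-sided, normal quantiles: (1.960 + 0.842)² × 2.318 = 18.2.
- One-sided, t-quantiles on 2 × (16 − 1) = 30 degrees of freedom: 15.09, rounded up to 16 per arm, which is the stated 32.

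Two-sided t-quantiles also give 16 (15.68), but only with the ICC set to 0. Since sidedness is open, both cases are shown below.

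**Error rate if the independent t-test is applied.** The true variance of the difference in means is DE times the variance the test uses. A nominal two-sided 5% test therefore has true error 2 × [1 − Φ(1.96/√DE)]. At the plan's ICC, √1.24 = 1.114 and 1.96/1.114 = 1.76, which gives an error of **7.8%**. A one-sided 5% test would have an error of about 7.0%.

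No ICC is given for the continuous outcomes, so the other rows are assumptions:

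| ICC | DE = 1 + 12 × ICC | 1.96/√DE | Two-sided error | Interval too narrow by √DE |
|---|---|---|---|---|
| 0.01 | 1.12 | 1.85 | 6.4% | 1.06 |
| 0.02 (plan, cessation) | 1.24 | 1.76 | 7.8% | 1.11 |
| 0.03 | 1.36 | 1.68 | 9.3% | 1.17 |
| 0.05 | 1.60 | 1.55 | 12.1% | 1.26 |

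**Check by simulation.** Normal outcomes in 32 pantries of mean size 13 with no true effect, 20,000 trials per setting. At ICC 0.02 the independent t-test rejected in 7.7% with equal pantries. With a cluster-size coefficient of variation of 0.31 it rejected in 8.1%. That coefficient matches 8/26 = 0.31 from the smokers per pantry in the Sample size section. A t-test on the 32 pantry means rejected in 4.9% and 5.0%. Allowing for clusters with 32 − 2 = 30 degrees of freedom therefore restores the level.

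**Baseline value.** The error formula contains no baseline term, so all of the inflation comes from the clusters. Adjusting for the t0 value removes roughly a share r² of the outcome variance, where r is the correlation between t0 and follow-up. The article gives no r. Assumed values of 0.5 and 0.7 give 25% and 49%.

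**The case against.** The strongest case on the other side has four parts.

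**The closing sentence comes after the clustered methods.** It can naturally be read as telling the analyst to treat secondary outcomes like the primary ones, with nesting included. The authors clearly know that clustering matters: they explain why pantries are randomised, assume an ICC and adjust both primary tests. A mixed model extends to a continuous outcome by changing the link. This stands. A reader might infer that the plan commits the continuous outcomes to the independent t-test and so to an 8% error rate. The documents do not support that; they leave the method open.

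**The t-test sentence may not concern outcomes.** It follows the descriptive statistics, and it pairs the t-test with an unadjusted chi-square test, whereas the next sentence gives the binary primary outcomes an adjusted one. A baseline or general comparison would remove that tension. This is plausible, but nothing in the text limits the sentence in that way.

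**A journal article may leave model detail to an analysis plan.** This is true of covariates and degrees of freedom. It answers less well the fact that the article names a test for continuous variables which, followed literally, does not suit the design.

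**The size is conditional.** The ICC of 0.02 was assumed for cessation, and two-sidedness is not stated. Hence the range. Cigarettes per day and FIES responses are also counts, so a linear model is not the only reasonable choice.

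**Conclusion.** The point holds as an ambiguity with a measurable consequence. The plan names no clustered method for a continuous outcome, names one unclustered test, and links the secondary outcomes to the rest of the section by a sentence that can be read more than one way.

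If the t-test is used, the two-sided error is about 7.8% at ICC 0.02, and about 6% to 12% for ICCs of 0.01 to 0.05. This rests on 13 participants per pantry, a two-sided test, and an ICC borrowed from cessation or assumed.

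Two further inferences would go too far. Omitting the t0 value does not contribute to the inflated error; it costs precision only. Nor do the main conclusions of the trial depend on this point, because both primary outcomes have a stated clustered analysis. The severity is therefore moderate.

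**What to change.** Replace the closing sentence on secondary outcomes with text such as:

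> Continuous secondary outcomes will be analysed with a mixed model with a random intercept for food pantry, arm as fixed effect, the t0 value of the outcome as covariate where collected, and small-sample (between-cluster) degrees of freedom, for example Kenward-Roger. If the distribution requires it, cigarettes per day and the number of affirmative FIES responses will be analysed with a count model that has the same cluster and baseline terms. Point prevalence of abstinence will be analysed with the logit mixed model used for the primary outcomes.

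Then confine the sentence on unadjusted t-tests and chi-square tests to description, or delete it. State whether body-mass-index is among the outcomes covered and whether it is measured at t0, since the Outcomes and Measures sections do not mention it. Point prevalence needs no t0 covariate, because every participant is a daily smoker at inclusion.

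The cost is wording only: no new measurement and no change to the sample size. The change is best made before outcome data are seen.

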## Objectives and hypotheses of the study

The main objective of the study is to investigate the impact of the smoking cessation measures on the smoking prevalence and on food security among food pantry users in Berlin.

The following primary hypotheses will be tested:
The percentage of individuals displaying continuous smoking abstinence 6 months after the treatment will be higher in the intervention condition compared to the control condition.The percentage of participants with an improved food security level 6 months after the treatment will be higher in the intervention condition compared to the control condition.The increased food security level will be mediated by continuous smoking abstinence.

Important secondary objectives include
to assess the impact of the smoking cessation measures on other measures of smoking status (point prevalence of smoking abstinence, the mean number of cigarettes smoked per day) and of food insecurity (the mean number of affirmative responses on the FIES) as well as on the health-related quality of life scores and body-mass-index;to investigate whether possible intervention effects are moderated by demographics (age, gender, migration status, socioeconomic status), the nicotine dependence and time perspective.

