#### Recruitment of participants

Participants will be recruited after randomisation of the food pantries. First, users of participating food pantries will be informed by posters and leaflets. In addition, food pantry users will be personally invited by trained study staff.

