### Outcome measures and evaluation

#### Measures

At t0, participants will be asked to complete a survey containing questions on demographics, developed by a previous study among food pantry users in Germany [41]; the Short Form 12 (SF-12) to measure the quality of life [42]; the quantity-frequency index [37]; the Fagerström Test for Nicotine Dependence (FTND) [39, 40]; the Food Insecurity Experience Scale (FIES) [43]; and the future, present-hedonistic and present-fatalistic subscales of the Zimbardo Time Perspective Inventory [44, 45]. At t1 and t2 continuous abstinence will be measured according to the “Russell standard” (“Have you smoked at all since [start date of last attempt to quit]?” “No, not a puff”; “1–5 cigarettes”; “More than 5 cigarettes?”) [46].

In addition, exhaled carbon monoxide will be measured at baseline as well as at t1 and t2. The time points for the measurements are shown in Table 1.

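### The named tests do not adjust for baseline although FIES, SF-12 and smoking quantity are measured at t0; this costs precision, mainly for the continuous secondary outcomes.

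*Protocol article*

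**What the plan says.** All locations are in the Protocol article.

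- **Statistical analyses, primary outcomes.** Hypotheses 1 (abstinence) and 2 (food security improvement) are tested with a chi-square corrected for the intraclass correlation. To handle nesting within pantries, "mixed models with the logit link function will be used to predict cessation and food security improvement". Covariates are neither listed nor ruled out.
- **Statistical analyses, other comparisons.** For differences between the arms, "independent t-tests for continuous variables and chi-square tests for categorical variables will be used". The section ends: "Secondary outcomes will be analyzed accordingly".
- **Measures.** The t0 questionnaire includes the FIES, the SF-12, the quantity-frequency index of smoking and the Fagerström test (FTND).
- **Outcomes.** Three of the secondary outcomes are continuous: cigarettes per day, the count of FIES items affirmed, and the quality-of-life scores. Each has a t0 counterpart.
- **Recruitment of participants.** "Participants will be recruited after randomisation of the food pantries". No stratification of the pantries is described.
- **Sample size.** "Assuming an intra-class correlation coefficient of 0.02, a 5% significance level, and 80% power, 32 clusters are needed to detect an effect", with 13 participants per pantry and cessation of 10% against 3%.

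**The concern.** A follow-up value usually depends strongly on the same person's starting value. Comparing follow-up means with a t-test leaves that explained variation in the error term. For food security improvement the dependence is built in: a participant who is food secure at t0 has no better category to reach, so the share improving in an arm depends partly on its baseline mix. With 32 pantries and no stated stratification, that mix can differ between arms by chance.

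A second issue lies in the same sentence. A t-test applied to individual participants treats people from one pantry as independent, although the sample size section assumes that they are not.

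At stake is precision in outcomes for which the needed covariate is already collected and, if the t-test wording is taken literally, the error rate of the continuous comparisons.

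**Working it through.** **Inputs from the article.** 16 pantries per arm, 13 per pantry (208 per arm), ICC 0.02, cessation 10% and 3%. In the Background, about 70% of pantry users in an earlier German study were food insecure, so about 30% were secure.

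**Inputs assumed.** Baseline to follow-up correlation r, food security improvement rates, and the prognostic strength of a baseline score for abstinence. The article gives none of these. The ICC of 0.02 is stated for the cessation calculation and is borrowed here for the other outcomes.

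**1. The plan's own figure.** Design effect = 1 + 12 × 0.02 = 1.24. With unpooled variance 0.10 × 0.90 + 0.03 × 0.97 = 0.1191 and t quantiles on 2 × (16 − 1) = 30 df, a one-sided 5% level gives (1.697 + 0.854)² × 0.1191 × 1.24 / (13 × 0.07²) = 15.09 pantries per arm, rounded up to 16, hence 32 clusters and 416 people. A two-sided level would need 19 or 20 per arm. The article does not state sidedness; that is a separate matter. No baseline covariate enters this calculation, so adjustment makes no part of it wrong.

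**2. Continuous secondary outcomes.** Adjusting for the t0 value multiplies the variance by 1 − r². Detectable standardised difference (two-sided 5%, 80% power) = 2.80 × √(2 × 1.24 × (1 − r²) / 208).

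| r (assumed) | Variance factor | Detectable difference | Power, adjusted, for an effect with 80% unadjusted |
|---|---|---|---|
| unadjusted | 1 | 0.306 | 80% |
| 0.3 | 0.91 | 0.292 | 83.6% |
| 0.5 | 0.75 | 0.265 | 89.9% |
| 0.6 | 0.64 | 0.245 | 93.8% |
| 0.7 | 0.51 | 0.218 | 97.5% |

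**3. Clustering ignored by a participant-level t-test.** True variance is 1.24 times what the test assumes. The effective critical value is 1.96 / √1.24 = 1.760, and 2 × (1 − Φ(1.760)) = 0.078. A nominal 5% becomes about 7.8%.

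**4. Food security improvement.** Take 30% secure at t0, unable to improve, and one improvement rate per arm among the insecure. For 20% against 30%, the overall rates are 14% and 21%.

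- Unadjusted variance term: 0.14 × 0.86 + 0.21 × 0.79 = 0.2863.
- Adjusted: 0.7 × (0.16 + 0.21) + (0.7 × 0.10² − 0.07²) / 2 = 0.2590 + 0.0011 = 0.2601.
- Ratio: 0.91.

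With an effective 208 / 1.24 = 167.7 per arm, power goes from 39.5% to 42.8%. For 15% against 25% the ratio is 0.93 (45.9% to 48.6%), and for 25% against 40% it is 0.87 (63.8% to 69.7%). The gain is about 3 to 6 points.

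A simulation with 22% improving in controls (500 trials per setting, generalised estimating equations, baseline mix 30/34/28/8%) gave 38.2% against 44.2–45.2%, and 65.6% against 68.8–73.0%. Type I error was 6.2% unadjusted and 5.6–5.8% adjusted. Closed-form unadjusted powers for those settings are lower (31% and 62%), so only the gain, about 3 to 7 points over both methods, should be used.

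**5. Chance imbalance in the food-secure share.** SD = √(2 × 0.30 × 0.70 × 1.24 / 208) = 5.0 percentage points. If 22% improve overall, 0.22 / 0.70 = 31% of the insecure do, so a one-SD imbalance moves the outcome by 0.05 × 0.31 = 1.6 points.

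**6. Abstinence.** Expected events are 20.8 + 6.24 = about 27. Adjusting for a baseline score with an odds ratio of 1.22 to 2.7 per SD gives variance ratios of 0.998 to 0.935 and moves two-sided power from 74.8% to between 74.9% and 77.5%.

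**The case against.** **The mixed models may include covariates.** The sentence on them gives only a purpose, and a covariate list is commonly left to an analysis plan. This stands: that sentence does not show an omission. The point rests on the chi-square and t-test sentences, where the named methods cannot take a covariate.

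**Plain t-tests for the secondary outcomes are not certain.** The t-test sentence follows the descriptive statistics, and the closing sentence on secondary outcomes comes after the clustered methods, so it may mean clustered models. This partly stands, and the 7.8% is therefore conditional on the literal reading. Even so, the only mixed model named has a logit link, which does not suit cigarettes per day or SF-12 scores, and no baseline term is named on either reading.

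**Baseline data are used.** A reader might infer that the trial makes no use of t0 values. The article does not support that: improvement is defined against the t0 category, missing values are carried forward from baseline, and nicotine dependence and demographics are planned moderators. None of these adjusts the treatment comparison, however.

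**Imbalance is not expected.** A reader might infer from recruitment after randomisation that imbalance is likely. Study procedure and Blinding say that staff and participants are blinded at the baseline assessment and that participants learn their pantry's allocation at the next visit. Imbalance is then a matter of chance, which a valid unadjusted test already allows for. A shift of 1.6 points is modest against the 7 to 11 points assumed in the simulation.

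**The gains rest on assumptions.** This stands. Also, the 30% food-secure share comes from pantry users in general, whereas the trial enrols daily smokers. The Background reports that smoking and food insecurity are related, so the share, and with it the gain for food security, may be smaller.

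**Conclusion.** The concern holds as an efficiency point. The tests named for the primary hypotheses and for continuous variables do not adjust for baseline, although the matching values are collected.

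- **Continuous secondary outcomes:** a clear loss, with variance 1.33 to 1.96 times what adjustment would give (1/0.75 to 1/0.51) at assumed r of 0.5 to 0.7. If the t-tests are run on individuals, there is also a type I error of about 7.8% at ICC 0.02.
- **Food security improvement:** a modest gain of about 3 to 7 power points, under assumed improvement rates and about 30% secure at t0.
- **Abstinence:** about 0 to 3 points. Everyone smokes daily at t0, so the outcome has no baseline variation of its own, and about 27 events support very few covariates.

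It would go too far to call the primary comparisons biased or the sample size wrong. An unadjusted test that allows for clustering remains valid, and the 32 clusters do not depend on adjustment.

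**What to change.** 1. **Cigarettes per day, FIES count, SF-12 scores:** replace the t-tests with linear mixed models that have a pantry random intercept and the t0 value of the same variable. This also settles the clustering question.
2. **Food security improvement:** add the baseline FIES raw score to the logistic mixed model. As a sensitivity analysis, fit the model among those food insecure at t0. Do not enter the t0 category as a factor: the food-secure stratum has no events, so its coefficient could not be estimated. The gains in step 4 of the working condition on the secure group exactly, so a single linear score may recover somewhat less in those scenarios.
3. **Abstinence:** FTND as a single covariate is optional.
4. **Primary hypotheses:** keep the ICC-adjusted chi-square and the unadjusted risk difference alongside the models, and state in advance which analysis decides each hypothesis.

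The cost is wording in the protocol or analysis plan, fixed before outcomes are analysed by arm, with no new data. One small downside is that an adjusted odds ratio is conditional on the covariate and should be shown beside the unadjusted risk difference.

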## Discussion

This study will increase understanding into the impact of a smoking cessation program targeted to food pantry users on smoking status and food insecurity.

In Germany, more than 940 “Tafel” food banks and food pantries provide food to around 1.65 million economically disadvantaged people [54]. In other affluent countries, such as the USA [55] and the UK [56], millions of people also rely on the assistance of food pantries and food banks. The results of this study might assist in the development and implementation of smoking cessation interventions for food pantry users in comparable countries.

Moreover, this study will investigate, for the first time, the long-term effects of manipulating smoking status on food insecurity. One of the few longitudinal studies examining smoking status and food insecurity demonstrated that, among smokers who were food secure at baseline, becoming food insecure was independently associated with lower likelihood of smoking cessation at the 12 year follow-up. Moreover, among non-smokers who were food secure at baseline, becoming food insecure was significantly associated with a higher likelihood of starting smoking at the 12 year follow-up, even when controlling for demographic variables including poverty [57].

The majority of people who started smoking after baseline were former smokers, indicating that food insecurity may increase the risk of relapse. Thus, food insecurity may not only be a consequence of smoking but also a risk factor for smoking relapse due to stress, hunger, or other factors related to food insecurity which smoking may alleviate [57]. The presented study aims to mitigate the impact of food insecurity on smoking relapse by involving food insecure participants in the development of a smoking cessation program. In the group sessions, known risk factors for relapse, such as food insecurity, will be addressed and participants will acquire strategies to cope with stress situations.

The results of this study will contribute to an enhanced understanding of the interplay between smoking status and food insecurity, and inform the practices of professionals who provide interventions to reduce the health risks in this population group, including social workers, psychologists and health professionals.

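### Carrying baseline forward for both abstinence and food security can make path B of the hypothesis 3 mediation model falsely positive

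*Protocol article*

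**What the plan says.** All references are to the protocol article.

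- **Objectives and hypotheses of the study.** The third primary hypothesis reads: "The increased food security level will be mediated by continuous smoking abstinence". It names no visit for the mediator.
- **Statistical analyses.** "To test hypothesis 3, a structural equation model will be used". Path A runs from arm to cessation, path B from cessation to food security improvement, and path C from arm to improvement. The model then asks whether the arm effect weakens once cessation is controlled for.
- **Statistical analyses, missing data.** "Missing values among the intention-to-treat population will be imputed using the baseline observation carried forward technique". Nothing exempts the mediation model.
- **Outcomes.** Both primary outcomes are set at 6 months (t2); the second is "increased food security level (the percentage of participants with an improved food security level) 6 months after the treatment has finished". Abstinence means "≤ 5 cigarettes since the start date of their last attempt to quit", confirmed by exhaled carbon monoxide (CO).
- **Study population.** Only daily smokers can enter.
- **Measures.** Continuous abstinence and CO are also recorded at t1, one month after the program. FIES and nicotine dependence are recorded at baseline.
- **Study procedure.** People not reached at the pantry get the follow-up questionnaire by post.
- **Discussion.** The authors write that "food insecurity may not only be a consequence of smoking but also a risk factor for smoking relapse".

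**The concern.** BOCF is often defended as cautious for abstinence, because a missing smoker stays a smoker. That defence does not carry over to an association between two outcomes. Carrying baseline forward makes a missing mediator not abstinent and a missing outcome not improved. A participant missing both therefore lands in the same cell every time, and the imputation itself links the two variables. Path B measures exactly that link.

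There is also a question of direction. On the natural reading, mediator and outcome are both classified at t2. The Discussion allows that food insecurity may promote relapse. A participant whose food security fails to improve and who then relapses would count in favour of path B.

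At stake is a primary hypothesis and the trial's most novel claim, that quitting improves food security. It rests on few people: at the planning rates, about 27 abstainers in all.

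**Working it through.** **Plan's own figures.** The article states no figure for hypothesis 3. Its sample size concerns cessation: 10% against 3%, 13 per pantry, intra-class correlation 0.02, design effect 1 + 12 × 0.02 = 1.24. The 16 pantries per arm reproduce with a one-sided 5% level and t quantiles (15.09, rounded up to 16). They are used here only for group sizes: 16 × 13 = 208 per arm, 416 in total. Expected abstainers: 208 × 0.10 + 208 × 0.03 = 27.04, which is 6.5% of 416.

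**Assumptions not in the article.** Dropout d of 20, 30 or 40%, equal in both arms and missing both variables. Improvement b of 30% among completers. Abstinence and improvement independent among completers, so true path B is zero. Abstinence after BOCF, a*, of 6.5%.

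**Step 1: sign of the artefact.** With completer rates a and b, the mean product after BOCF is (1 − d)ab and the product of the means is (1 − d)²ab. The covariance is ab·d(1 − d), which is positive whenever there is any dropout. No difference in dropout between arms is needed.

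**Step 2: size.** Every abstainer is a completer, so improvement among abstainers is b. All dropouts fall among non-abstainers, whose improvement rate is b(1 − d − a*)/(1 − a*). The false difference is b·d/(1 − a*).

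| d | Improved, abstinent | Improved, not abstinent | Difference | Odds ratio |
|---|---|---|---|---|
| 20% | 30% | 0.30 × 0.735/0.935 = 23.6% | 6.4 points | 1.39 |
| 30% | 30% | 0.30 × 0.635/0.935 = 20.4% | 9.6 points | 1.67 |
| 40% | 30% | 0.30 × 0.535/0.935 = 17.2% | 12.8 points | 2.07 |

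With improvement of 20% or 40% instead, the odds ratio at 30% dropout is 1.59 or 1.79.

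**Step 3: how often path B is significant.** In 4,000 simulated trials (208 per arm, no clustering), improvement was regressed on arm and abstinence with robust standard errors.

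| Dropout | Mean false difference | Path B significant |
|---|---|---|
| 0% | 0.0 points | 6.8% |
| 20% | 6.4 points | 9.7% |
| 30% | 9.9 points | 17.3% |
| 40% | 13.1 points | 28.6% |

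The 6.8% without dropout is not due to BOCF. If 10% and 3% are completer rates instead, the bias is of the same size (at 30% dropout, 0.09/(1 − 0.0455) = 9.4 points), but path B is significant in only 9, 11 and 17% of trials at 20, 30 and 40% dropout. A logistic version, counting only positive results at a nominal 2.5%, gave about 13, 24 and 39%.

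**Step 4: postal returns.** Suppose 30% do not attend and half of them return a FIES by post without CO. Their abstinence is still set to no, but their food security is real. Improvement among non-abstainers becomes 0.30 × (0.635 + 0.15)/0.935 = 25.2%. The false difference falls to 4.8 points (odds ratio 1.27), and in simulation path B is significant in about 8% of trials, against 6 to 7% with no attrition. If all return a FIES, the difference is zero.

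**Step 5: path C.** With equal dropout and no true effect, improvement after BOCF is b(1 − d) in both arms, for example 0.30 × 0.70 = 21%. Path C stays null. In 3,000 simulated trials, paths A, B and C were all positive and significant in 0.2, 0.2 and 0.8% at 20, 30 and 40% dropout. Paths A and B together were significant in 8, 13 and 23%, against about 2% without dropout.

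**The case against.** Four points can fairly be made in the plan's defence.

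- **Postal follow-up.** Not every non-attender misses both variables. This stands. Step 4 shows that it can halve the false difference and bring significance close to its no-dropout level, so the main figures are an upper case. The artefact disappears only if every non-attender returns a FIES.
- **Path C.** A reader might infer that missing-data coding alone could establish mediation. The article does not support that. It lists path C and attenuation as well as A and B, and path C stays null under equal dropout. How much is at risk depends on whether support for hypothesis 3 requires path C, and the article does not give that rule.
- **Timing.** A reader might take it as stated that mediator and outcome are both t2 variables, or that food insecurity causes relapse. The first is inferred from the outcome definitions, and the Discussion says only that it may. Abstinence also looks back to the quit date, so it is not purely concurrent. It is still classified at t2, however, and that does not exclude the reverse path.
- **Clustering and covariates.** A reader might conclude that the mediation model ignores clustering. The article adjusts the tests of hypotheses 1 and 2 for intraclass correlation and uses mixed logit models for both cessation and food security improvement. The mediation sentence is merely silent. Model details, including covariates, are commonly left out of an article, so this silence is not an error.

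The BOCF rule differs from these because the article states it for all missing values.

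**Conclusion.** The concern holds for the combination of BOCF and the mediation model. Applied to both variables, BOCF biases path B upwards by arithmetic, even with equal dropout and no true association. With 30% improvement among completers and 20, 30 or 40% missing both variables, the false difference is about 6, 10 or 13 points and path B is significant in about 10, 17 or 29% of trials, against about 7% without dropout. The dropout and improvement rates are assumptions: the article names attrition bias as a risk but gives no rate.

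The effect reaches the joint reading of paths A and B, not the total effect. Separately, on the natural t2-to-t2 reading, path B should not be taken as directional on its own. The documents do not support a claim that clustering is ignored, that reverse causation is established, or that coding alone would prove full mediation.

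**What to change.** For the hypothesis 3 model only:

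1. Replace joint BOCF with multiple imputation that respects pantry clustering and has arm, abstinence and food security in the imputation model. Keep BOCF as a sensitivity analysis. The rule for hypothesis 1 need not change on this account.
2. Adjust the mediator and outcome equations for baseline FIES and nicotine dependence. Abstinence is not randomised, and baseline food security limits the room to improve.
3. State which visit supplies the mediator, and add a sensitivity model with t1 abstinence as mediator and t2 food security as outcome. This does not cure the BOCF problem by itself, so step 1 is needed as well.
4. Say in one sentence how the model handles pantries.

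No new data are needed. The costs are more analysis work and reliance on a missing-at-random assumption, which the retained BOCF analysis helps to probe. Abstinence at t1 is a shorter exposure than at 6 months, so that model may dilute the indirect effect. This is why it is proposed as a sensitivity analysis and not as a replacement.
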